#### Measurements

Primary outcome measure of the randomized trial is weight in kilograms. Secondary outcome measures are energy expenditure, glycated hemoglobin, binge eating, self-efficacy in eating and weight control, body satisfaction, healthy habit formation, disordered eating-related behaviors and cognitions, psychopathological symptoms and weight-related quality of life. Data will be collected at baseline, at discharge from the hospital (c.a. 1 month after) and after 3, 6 and 12 months from the end of the in-hospital treatment.

##### Height and weight

Height will be measured with a stadiometer and weight will be assessed with the participant in lightweight clothing with shoes removed on a balance beam scale. Data collected at follow-up time points will be self-reported. Weight and height will be used to calculate BMI (weight in kilograms divided by the square of height in meters).

##### Energy expenditure

Energy expenditure is estimated using a multisensory armband (SenseWear^® ^Pro_2 _Armband, BodyMedia, Inc.). A proprietary heat-flux sensor measures the amount of heat being dissipated by the body by measuring the heat loss along a thermally conductive path between the skin and a vent on the side of the armband. Skin temperature and near-armband temperature are also measured by sensitive thermistors. The armband also measures galvanic skin response (GSR - the conductivity of the wearer's skin) which varies due to physical and emotional stimuli. A two-axis accelerometer tracks the movement of the upper arm and provides information about body position. The armband also contains a radio and a data port, allowing both wireless transmission and communication as well as wired downloading of data. SenseWear^® ^Pro_2 _Armband is a cost-efficient and simple solution that can be applied outside the laboratory in a free-living environment to track energy expenditure, physical activity durations and levels, and lifestyle information. For more detailed information on the armband and the algorithms it implements, visit the web-site http://www.armband.it.

##### Glycated hemoglobin

According to the Consensus Statement on the Worldwide Standardization of the Hemoglobin A1C Measurement [38], the hemoglobin A1C (A1C) assay has become the gold-standard measurement of chronic glycemia for over two decades. Anchored in the knowledge that elevated A1C values increase the likelihood of the micro-vascular complications of diabetes (and perhaps macro-vascular complications as well), the assay has become the cornerstone for the assessment of diabetes care. In this study, we adopt the measurement method (concentration of only one molecular species of glycated A1C) and results reporting (mmol/mol and derived NGSP %) developed by the International Federation of Clinical Chemistry and Laboratory Medicine (IFCC) [39].

### Psychological and behavioral questionnaires

Participants will complete the following questionnaires at entry to the study, at discharge from the hospital and at 3, 6 and 12-month follow-up time points by postal mail, Differently, the Outcome Questionnaire will be administered electronically through the web-platform before each videoconference session with the clinical psychologist.

#### The Self-Report Habit Index (SRHI) - Italian translation

The SRHI is a measure of the development and strength of habits. It has a stem " [the behavior] is something that ..." followed by 12 items such as "I do without thinking'. The SHRI has high internal consistency (α > 0.9), high test-retest reliability (r = 0.91) and high convergent and discriminative validity [40]. In our study, behaviors are: "eating in accordance with the prescribed diet" and "undertaking regular physical activity".

#### Weight Efficacy Life Style Questionnaire (WELSQ) - Italian version

The WELSQ is composed of 20 items that measure the confidence of the subjects about being able to successfully resist the desire to eat. The questionnaire was used to predict both weight loss and weight loss maintenance across a range of ages in men and women [21].

#### Body Uneasiness Test (BUT) - Italian version

The BUT is a self-report inventory that measures body uneasiness by a global severity index and five sub-scales: Weight Phobia, Body Image Concerns, Avoidance, Compulsive Self-Monitoring, Depersonalization [41].

#### Binge Eating Scale (BES) - Italian version

The BES is a short self-report questionnaire which measures severity of binge eating [42]. The Italian version of the instrument [43] consists of 16 items, which are composed by three or four sentences about the severity of binge eating. Cut-off score for mild binge eating symptoms is 17; scores between 18-26 indicate moderate binge eating symptoms and scores over 27 can be associated with a severe binge eating disturbance.

#### Eating Disorder Inventory (EDI-2) - Italian version

The EDI-2 is a widely used, standardized, self-report measure of psychological symptoms commonly associated with anorexia nervosa, bulimia nervosa and other eating disorders. The EDI-2 does not yield a specific diagnosis of eating disorder. It is aimed at the measurement of psychological traits or symptom clusters presumed to have relevance to understanding and treatment of eating disorders. The EDI-2 consists of 11 subscales derived from 91 items. Three of the subscales were designed to assess attitudes and behaviors concerning eating, weight and shape (Drive for Thinness, Bulimia, Body Dissatisfaction) and the remaining eight ones tapped more general constructs or psychological traits clinically relevant to eating disorders (Ineffectiveness, Perfection, Interpersonal Distrust, Interoceptive Awareness, Maturity Fears, Asceticism, Impulse Regulation and Social Insecurity) [44,45].

#### Symptom Check List (SCL-90) - Italian version

The SCL-90 is a brief, multidimensional self-report inventory designed to screen for a broad range of psychological problems and psychopathological symptoms. It consists of 9 symptom scales (Somatization, Obsessive-Compulsive, Interpersonal Sensitivity, Depression, Anxiety, Hostility, Phobic Anxiety, Paranoid Ideation and Psychoticism) and 3 global indices [46].

#### Impact of Weight on Quality of Life-Lite (IWQOL-Lite) - Italian version

IWQOL-Lite is the short version of the original IWQOL and is composed by 31 items. The questionnaire is self-report and consists of 5 scales assessing the impact of weight on QoL-related factors such as Physical Functioning, Self-Esteem, Sexual Life, Public Distress and Work. IWQOL-Lite has shown high internal consistency and high test-retest reliability [47,48]

#### The Outcome Questionnaire (OQ 45.2) - Italian translation

The OQ 45.2 is an self report questionnaire developed by Michael Lambert in 1996 [35]. The OQ 45 items version is a measure of outcome and it is designed in order to collect repeated measures of patient progress during therapy and after its conclusion. This instrument is one of the most used in psychotherapy research in the U.S. [49]. The OQ 45.2 is composed by 45 items that form 3 scales: Symptom Distress (SD), Interpersonal Relations (IR) e Social Role (SR), and a Global Index.

### Statistical analysis

Descriptive statistics (means ± SD, or median and interquartile ranges, as appropriate) will be used to describe the study sample with regard to baseline characteristics. Before selecting the most appropriate statistical tests, assumptions for parametric analyses will be checked. Repeated-measure ANCOVA will be used in order to evaluate the effects of the intervention when data do not violate the parametric assumptions. The mean differences between intervention and control group with 95% confidence intervals will be calculated. Analyses will be adjusted for possible confounders such as gender and age. Also effect modification will be investigated using interaction terms between intervention group and gender and age, respectively. If data violate parametric assumptions, we will use the exact methods with Monte Carlo approximation, a series of non-parametric statistical algorithms that enable researchers to make reliable inferences when data are sparse, heavily tied or unbalanced, not normally distributed, or fail to meet any of the underlying assumptions necessary for reliable results using the standard asymptotic method [50]. The Mann-Whitney test with Monte Carlo approximation will be used for independent measures, the Wilcoxon rank-sum test for repeated measures and the Fisher exact test for categorical variables. Weight data will be analyzed with an intention-to-treat (ITT) approach with dropouts assumed to have regained 0,3 kg per month, an assumption already used in previous studies [12,51]. Differently, missing data in the other variables will be replaced with baseline observation carried forward (BOCF) or last observation carried forward (LOCF) as appropriate, assuming no improvement for non-responders patients. Odds ratios with 95% confidence intervals will be also calculated at each follow-up time-point with respect to: 1) the percentage of participants maintaining or improving weight lost at discharge and 2) the percentage gaining a 5% and a 10% of baseline weight reduction for the TECNOB group in comparison with the control group. Finally, logistic regression will be used in order to find out predictors of treatment success defined as weight loss maintenance at the final follow-up time-point.

A confirmatory statistical test with alpha = 0,05 two-sided will be used for the primary outcome (weight loss in Kilograms), whereas explorative statistical tests will be used for all the secondary outcomes. Given the exploratory feature of the latter tests, critical alpha will be maintained at 0,05 two-sided without any correction for multiple comparisons.

All data analyses will be performed using the Statistical Package for the Social Sciences (version 12.0; SPSS, Inc., Chicago, IL).

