#### Sample size calculation

The sample size calculation is based on a difference in weight regain of 3 kg between the intervention and control group after 12 months. The standard deviation of weight regain for the control group is considered to be 6 [12]. Based on these data, 64 participants per group are needed to detect this difference with an alpha of 0.05 two-sided and a power of 0.80. We decided not to make assumptions on sidedness because the TECHNOB program may also have negative effects in comparison with the control group. A sample of 154 persons (n = 77 per group) is required taking into account a dropout rate of 20%.

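### The primary outcome is named three ways, and the stated 80% power belongs to a 12-month comparison of regain that is not tied to the confirmatory test, so that test's power is not established

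*Protocol article*

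**What the plan says.** The article describes the outcome behind its only confirmatory test in three ways.

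- **Measurements** (and the Abstract): "Primary outcome measure of the randomized trial is weight in kilograms". No time point is attached.
- **Statistical analysis**, where the two-sided alpha of 0.05 is assigned: the confirmatory test "will be used for the primary outcome (weight loss in Kilograms").
- **Sample size calculation**, which turns to regain: "The sample size calculation is based on a difference in weight regain of 3 kg between the intervention and control group after 12 months". Its spread is also that of regain: "The standard deviation of weight regain for the control group is considered to be 6". The result is that "64 participants per group are needed to detect this difference with an alpha of 0.05 two-sided and a power of 0.80".

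For the model, Statistical analysis says "Repeated-measure ANCOVA will be used in order to evaluate the effects of the intervention", provided parametric assumptions hold, with rank tests otherwise. On covariates: "Analyses will be adjusted for possible confounders such as gender and age". It names no dependent variable, visit or contrast (group main effect, group-by-time interaction or 12-month difference) and mentions neither baseline nor discharge weight as a covariate. Weight is collected at baseline, at discharge, and 3, 6 and 12 months after discharge.

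**The concern.** Weight, loss and regain are different variables. Regain runs from discharge. Loss would ordinarily run from baseline. Weight has no reference point. The article itself uses both reference points in its secondary responder definitions (weight lost by discharge, and a percentage of baseline weight), so the choice between them is a real one. The alpha is attached to one variable and the power to another, and the model is attached to neither.

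Two things are at stake. First, a reader cannot tell what power the confirmatory test has. Second, the outcome, reference visit and contrast can still be chosen after the data are seen, for the one test that is meant to be confirmatory.

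**Working it through.** **1. Reproduce the plan's figure.** Inputs from Sample size calculation: difference 3 kg, SD 6 kg, two-sided alpha 0.05, power 0.80.

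Normal approximation: n = 2 × (1.960 + 0.842)² × 6² / 3² = 2 × 7.85 × 4 = 62.8, so 63 per group. The two-sample t-test gives 63.77, so 64. Power at 64 is 0.801. The arithmetic is right for an unadjusted comparison of two group means of 12-month regain.

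**2. Does the expected difference change with the outcome label?** At 12 months, no. Randomization follows baseline and both arms get the same in-hospital programme. If allocation does not affect the hospital phase, the expected arm difference is 3 kg for weight, for loss and for regain. What changes is the SD.

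**3. Power at 64 per group for 3 kg at 12 months, by outcome.** Two-sample t-test with d = 3/SD. The SDs of loss and of weight are not in the document and are assumed.

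| Outcome tested | SD (kg) | Power |
|---|---|---|
| Regain from discharge (as powered) | 6 | 0.80 |
| Loss from baseline | 5 / 6 / 7 / 8 | 0.92 / 0.80 / 0.67 / 0.56 |
| Loss from baseline, in-hospital change SD 2.5 added independently to regain | √(6² + 2.5²) = 6.5 | 0.74 |
| Raw 12-month weight, baseline weight not in model | 15 / 20 / 25 | 0.20 / 0.13 / 0.10 |

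**4. Baseline weight as covariate.** Assume equal SD s at baseline and 12 months. Then r = 1 − SD²(change)/(2s²) and residual SD = s√(1 − r²). The change here runs from baseline, so its SD must be the baseline-to-12-month SD. With 6.5 kg and s = 20: r = 1 − 42.25/800 = 0.947, residual SD 6.41, power 0.75. Across s = 15 to 25 the residual SD is 6.35 to 6.44 and power is 0.76 to 0.74. If the correlation is varied freely instead, with s = 20 and r = 0.90 / 0.95 / 0.97, power is 0.49 / 0.77 / 0.93.

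**5. Contrasts within a repeated-measures model.** Take change from discharge at 3, 6 and 12 months with 12-month SD 6, under two assumed covariance forms: (i) equal SD at each visit with correlation 0.5 to 0.9, so the SD of the three-visit mean is 6√((1 + 2ρ)/3) = 4.90 to 5.80; (ii) variance growing in proportion to time, which gives 3.87.

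- Effect builds linearly (0.75, 1.5, 3 kg): the average is 5.25/3 = 1.75 kg. Power of the group main effect is 0.40 to 0.72, and of the group-by-time test 0.47 to 0.99.
- Effect constant at 3 kg: power of the main effect is 0.83 to 0.99, and of the group-by-time test 0.05.

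So which contrast is tested, and how the effect develops, move power to either side of 0.80.

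**The case against.** The strongest reply is that this is a condensed article and the contrast may be fixed in a fuller document. Much of that reply stands.

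- **Covariates.** The list is open (gender and age are examples), and an ANCOVA commonly includes the baseline value. Not naming baseline weight is weak evidence taken alone, and a reader should not infer that it has been excluded.
- **Very low power.** A reader might infer that the trial has 10 to 20% power. That needs a test of raw 12-month weight without baseline weight, plus an assumed SD of 15 to 25 kg. The alpha is attached to weight loss, a within-patient change, so the document does not commit to such a test.
- **Averaging over visits.** A reader might infer that the confirmatory test is a group effect averaged over all five time points, including two at which the arms have had the same care. The text does not say so. A group-by-time test or a 12-month contrast fits it equally well, and if the variable is loss, baseline cannot be an outcome level.
- **Adjustment as a cure.** A reader might infer that adding baseline weight brings power back to about 0.81–0.82. That figure puts the discharge-to-12-month SD of 6 in place of the baseline-to-12-month SD. Allowing 2.5 kg for in-hospital change gives 0.74 to 0.76.

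What the reply does not answer is the contradiction within the article: three outcome names, with the alpha on one and the power on another. A fuller plan would have to choose among them; it cannot agree with all three.

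**Conclusion.** The point holds as a mismatch between the powered quantity and the confirmatory test. The 80% at 64 per group is correct for an unadjusted comparison of 12-month regain with SD 6, and no part of the article connects that comparison to the repeated-measures ANCOVA or to weight loss. Power of the confirmatory test is therefore not established. It is not shown to be below 80%.

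For the most natural reading, loss from baseline at 12 months, the shift is likely to be modest: 0.74 if an in-hospital SD of 2.5 kg adds independently, and 0.92 to 0.56 over SDs of 5 to 8 kg. A time-averaged group effect would have less power if the effect builds up over time and more if it is constant. All these figures apart from the 0.80 rest on assumed SDs, correlations and time courses. The textual mismatch needs no assumption.

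**What to change.** Use one definition of the primary outcome in the Abstract, Measurements, Sample size calculation and Statistical analysis. Define the confirmatory test as the between-arm difference in weight at 12 months after discharge, from a repeated-measures model with arm, visit, arm-by-visit interaction, baseline weight, sex and age, at two-sided 0.05. Make the 3- and 6-month contrasts, the time-averaged effect and the definitions using another reference point secondary.

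In Sample size calculation, say that the 80% was computed for regain with SD 6, and restate power for the chosen outcome from an SD (or residual SD) of that same quantity. Do not state that covariate adjustment secures 80%.

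The cost is wording and one recalculation. Weight is already collected at every visit the model needs. If the restated power falls short of 0.80, the sponsor must decide whether to accept that or revisit the sample size.

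### The plan names an independent-samples test for repeated measures, and lets a check of the outcome data choose the confirmatory between-arm test

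*Protocol article*

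**What the plan says.** All the text at issue is in the protocol article, mostly under Statistical analysis.

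- Rule for choosing the test: "Before selecting the most appropriate statistical tests, assumptions for parametric analyses will be checked".
- Parametric branch: "Repeated-measure ANCOVA will be used in order to evaluate the effects of the intervention when data do not violate the parametric assumptions". The section also promises mean differences with 95% confidence intervals, adjustment for confounders such as gender and age, and interaction terms with both.
- Fallback branch: "If data violate parametric assumptions, we will use the exact methods with Monte Carlo approximation". Two tests follow: "The Mann-Whitney test with Monte Carlo approximation will be used for independent measures", and "the Wilcoxon rank-sum test for repeated measures".
- Missing weights: an intention-to-treat analysis with "dropouts assumed to have regained 0,3 kg per month".
- Confirmatory claim: "A confirmatory statistical test with alpha = 0,05 two-sided will be used for the primary outcome (weight loss in Kilograms". The test is not named, and the primary outcome is not exempted from the selection rule.
- Outcome scale: under Measurements, "Primary outcome measure of the randomized trial is weight in kilograms". The Statistical analysis section calls it weight loss, and the sample size section works with weight regain.

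**The concern.** There are two separate problems.

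First, the Wilcoxon rank-sum and Mann-Whitney tests are one test, and it assumes two independent groups. The plan therefore gives the same test two names and assigns one of them to data where each patient is their own comparator. An analyst who follows the text discards the pairing. Monte Carlo p-values do not repair this, because they change how the p-value is computed and not what the test assumes.

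Second, the single confirmatory test is settled only after the outcome data have been examined. The plan does not say which check, which threshold, which scale or time point, or whether the check comes before or after imputation. The branches are not interchangeable. Mann-Whitney takes no gender and age adjustment or interaction terms, does not model the repeated visits, and does not itself return a mean difference in kg with a confidence interval. The imputation also adds artificial structure to the data being checked, so the switch can be triggered by imputed values rather than by patients.

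**Working it through.** **The plan's own figure.** The sample size section gives a difference of 3 kg, SD 6 kg, two-sided alpha 0.05 and power 0.80. The normal approximation is n = 2 × (1.960 + 0.842)² × 6² / 3² = 62.8, so 63 per group. The t-test calculation gives 63.77, so 64, with power 0.801. The stated 64 is reproduced, and nothing below changes it.

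**Step 1: rank-sum against signed-rank on paired weights.** From the plan: n = 77 per arm and an SD of 6 kg, taken here as the SD of within-patient change. Assumed: a true within-arm change of 3 kg, and a between-patient weight SD *s* of 12 to 25 kg, because the document gives none. Since Var(change) = 2s²(1 − ρ) = 36, ρ = 1 − 36/(2s²).

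| s (kg) | ρ | rank-sum power | signed-rank power |
|---|---|---|---|
| 12 | 0.875 | 0.128 | 0.989 |
| 15 | 0.920 | 0.016 | 0.987 |
| 18 | 0.944 | 0.001 | 0.978 |
| 20 | 0.955 | 0.000 | 0.987 |
| 25 | 0.971 | 0.000 | 0.991 |

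With no true change, rank-sum rejected in none of the simulated samples, and signed-rank in 4.4 to 5.4%.

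A rough normal calculation shows why. At s = 12 the independent-samples standard error is 12 × √(2/77) = 1.93 kg, while the true standard error of the mean change is 6/√77 = 0.68 kg. The statistic centres on 3/1.93 = 1.55 with SD 0.68/1.93 = 0.35. It must reach 1.96, which is (1.96 − 1.55)/0.35 ≈ 1.2 SDs away, so it does so about 12% of the time. At s = 20 the standard error is 3.22 kg, the centre 0.93 and the SD 0.21, so the threshold is nearly 5 SDs away.

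**Step 2: does the branch matter for the confirmatory comparison?** A t-test stands in for the parametric branch. With 20% of values imputed at +3.6 kg, 77 per arm and a true 3 kg effect, power is 0.77 for the t-test and 0.73 for Mann-Whitney. Each keeps its type I error near 0.05. The two disagree on significance in about 7 to 9% of trials.

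**Step 3: can the imputation trip the check?** A patient lost at discharge is imputed at 12 × 0.3 = +3.6 kg, the same for everyone. A patient lost after month 3 or month 6 gets an individual last weight plus 9 × 0.3 = 2.7 kg or 6 × 0.3 = 1.8 kg, so there is no common value. The planned 20% of 77 is about 15 patients per arm. Uncensored regain was taken as exactly normal with SD 6 kg, so rejections above the nominal level come from the imputation. Normality tests were run at 0.05; the plan names neither test nor level.

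| Scale and dropout timing (20% dropout) | Normality rejected |
|---|---|
| Regain, all lost at discharge, pooled residuals with a 3 kg arm difference | 54–72% (Shapiro-Wilk) |
| Regain, all lost at discharge, one sample of 77 | 56–63% (Shapiro-Wilk), 86–87% (Lilliefors) |
| Regain, all lost at discharge, one sample of 154 with a common mean | 84–95% (Shapiro-Wilk) |
| Regain, loss spread over follow-up, one sample of 77 | 11–17% (either test) |
| Regain, loss spread over follow-up, both arms pooled | about 15–34% (both tests and both layouts) |
| Raw weight, assumed SD 18 kg, either timing | about 3–7%, near nominal |

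The answer therefore depends on scale and timing, and the plan fixes neither the scale of the check nor its place before or after imputation. If sphericity is also checked, its rejection rate rises from 5% to 16% at 20% dropout under compound symmetry. If variance grows over time, sphericity is rejected even with no imputation.

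**The case against.** **A slip of one word.** The sentence contrasts independent with repeated measures, so a paired test was clearly meant. That is very probably right. The error as written also cannot create a false positive, and within-arm change does not decide the trial. What stands is that the text names the wrong test and should be corrected.

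**Detail for the analysis plan.** Both branches are named in advance, and the criterion for the check may sit in a document not shown. Silence on the criterion alone would not be a finding. But the article states a rule, that the data choose the test, and applies it without exempting the confirmatory comparison. A criterion would make the rule reproducible, yet the estimand and adjustment would still depend on its outcome.

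**Small effect.** Power of 0.77 against 0.73, with nominal type I error for each test, is a modest difference. This is fair, and it limits the severity. Disagreement in about one trial in eleven to fourteen still matters for a single confirmatory claim.

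**Stronger readings to avoid.** A reader might infer that the imputation is likely to fail the check, making Mann-Whitney the branch most likely to be used. That needs nearly all dropouts to leave at discharge and a check on regain or baseline-adjusted residuals. With visits at 3, 6 and 12 months, losses spread over follow-up are at least as plausible, and rejection is then less likely than not at 20% dropout. On raw weight, the named primary outcome, it stays near nominal. A reader might also say that the fallback drops baseline weight, but the plan lists only gender and age as examples of adjusters. Nor does the plan abandon the mean difference: it promises one without restricting it to the parametric branch. Mann-Whitney simply does not supply it.

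**Conclusion.** Both parts hold, at moderate weight.

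1. The test named for repeated measures is wrong on the face of the text. Followed literally, it would miss almost every real within-arm change of 3 kg. This rests on an SD of change of 6 kg and an assumed weight SD of 12 kg or more. The consequence is confined to within-arm comparisons and is conservative.
2. The confirmatory between-arm test is left to a check of the outcome data. The 7 to 9% disagreement assumes a true 3 kg effect and uses a t-test in place of the full repeated-measure ANCOVA, so it indicates the size rather than measuring it exactly.

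The imputation is an aggravating factor, not a certainty. It can trigger the switch, and how often depends on the scale checked and when patients leave.

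**What to change.** Two sentences in the plan:

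- In the non-parametric paragraph, replace rank-sum with the Wilcoxon signed-rank test for repeated measures, keeping Mann-Whitney for independent groups.
- State that the confirmatory test is the 12-month between-arm contrast from the covariance-adjusted model, with baseline weight as a covariate alongside those already named, whatever the normality check shows. If residuals are non-normal, use a bootstrap or robust-variance confidence interval. Report Mann-Whitney on the change score as a sensitivity analysis only.

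With baseline weight in the model, 12-month weight and change from baseline give the same arm contrast, so this also settles the scale between those two descriptions of the outcome. The promised mean difference in kg and the gender and age adjustment are kept in every case. No extra data or patients are needed.
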